### Sample size

We hypothesized that the prevalence of the primary endpoint - severe lung impairment at 24 months period of follow up after TB diagnosis (conservative estimation based on a literature review) will be 15%. A sample size of 1.600 patients allows the estimation of the primary end point in the total cohort with a precision (half width of the 95% confidence interval) of about 1.75%. In addition, the prevalence within specific subgroups can be estimated adequately, e.g. with a precision between 2.5 and 7.8% in subgroups with a proportion of 50% (e.g. HIV) and 5% (e.g. diabetes) of the total cohort, respectively. Moreover, based on a pre-set alpha of 5% (two-sided) the sample size allows the detection of risk factors causing a duplication of the prevalence of severe lung impairment with a power of at least 80%, even for risk factors with a low prevalence of 5% in the total cohort. Depending on the availability and quality of patient’s end-point data, or if the prevalence of the primary outcome is less than 15%, it may be necessary to recruit more or less participants into the study.

### Recruitment and screening

Recruitment takes place at the research sites and health care facilities through collaboration with National TB Program (NTP), and in the communities which might be enhanced by individual and community awareness through advertisement, posters, radio announcements, and community sensitization campaigns. Each study site implements its own strategy to enhance recruitment.

### Study procedures

Clinical and pulmonary assessments, biological sample collections and collection of socio-economic data will be performed according to the pre-defined SOE. All enrolled patients will be treated within the NTP and receive anti-TB treatment according to the local national guidelines.

#### Clinical assessments and procedures

We will assess the pulmonary outcome, co-morbidities and clinical risk factors using a number of methods. These include: spirometry using the EasyOne or EasyOnPC (ndd Medical Technologies, Inc., Zurich, Switzerland), Electrocardiogram (ECG), 6 min walking test (6MWT), chest X-ray, St. George’s respiratory questionnaire, blood analysis (haematology, biochemistry including HbA1c, HIV/CD4, hepatitis B), urinalysis and risk-factors questionnaires (risk behaviour, environmental and occupational risk factors, among others). In addition, household air pollution is estimated by measuring participant’s breath carbon monoxide (CO) output (exhaled CO levels), which is collected using a handheld breath CO monitor - The Micro+™ Smokerlyzer® (Bedfont® Scientific Ltd., UK).

#### Laboratory procedures and testing

All laboratory procedures (apart from some specific assays planned for investigation of host-immune response or pathogen characteristics not locally available) will be performed at each study site and at the designated site laboratories under the supervision of the study principal investigators and using unified standard operating procedures. In the study TB labs we will carry out standard TB diagnostic procedures including smear, Xpert MTB/RIF or Ultra assay (Cepheid Inc., USA), liquid and solid culture, drug resistance testing in culture and molecular speciation testing. For analysis of pathogen-related risk factors, we will perform a number of pilot studies including characterization of MTB strains by next generation whole genome sequencing, identification of mixed infections and minority subpopulations as well as capture the bacterial load, e.g. using molecular methods to monitor treatment response. A number of different assays will be performed to study in detail the host response to TB treatment and individual predisposing risk factors for long term lung outcome on stored samples, such as (but not limited to) sputum and whole blood transcriptomics, flow cytometry, cytokine assays and host-genetic analysis.

#### Assessments related to socio-economic consequences and quality of life

All patients will be interviewed by trained study staff using a novel version of the WHO’s generic TB patient cost survey instrument [27] which has been adapted for both the longitudinal study design and local context of each setting. The instrument includes questions about direct out-of-pocket costs (net of reimbursement) of medical care, transport, food and accommodation during health seeking, indirect costs such as income loss and socio-economic coping mechanisms (e.g. taking a loan, selling assets or property or taking children out of school). Moreover, the instrument collects information about health insurance coverage and reimbursements and social welfare or paid sick leave received. A standardized short-form 36 item health survey (SF-36) combined with a PIQ-6™ (4 items) will simultaneously measure overall health, pain severity and the impact on functional health and well-being. In addition to the above we will also be using the Sheehan Disability scale (5 items) to assess health status impairment associated with TB and Kessler Psychological Distress scale (K10), a 10 item questionnaire, to measure distress based on questions about anxiety and depressive symptoms. These are all standardized validated questionnaires that have been widely used in TB studies and are simple to administer and repeatable over time. The patient cost and quality of life questionnaires will be completed at baseline and at pre-defined visits (e.g. 2, 6, 12 and 24 months). Health system costs will be based on actual patient usage with unit costs assigned, but will be collected later for the 24 month period. Resource utilization and treatment outcomes will be collected using clinical records, health facilities records, price lists and reports.

### Sample collection and storage

Blood, sputum and urine specimens are obtained from each patient at different time points for analysis and storage. The SOE is aligned with The RePORT International cohort and other TB cohorts to enable future research collaborations with other TB research consortia and facilitate comparability of outcome data across different cohorts. The researchers who manage or have access to human specimen data are legally and ethically obliged to protect these data according to international standards. Specific samples, e.g. TB strains, will be shipped to collaborating institutions and stored in their laboratories for further analysis.

Stored specimens will also be accessible for evaluation of future emerging TB diagnostics, genetic markers and biomarkers, provided informed consent and ethical approval for future use are available. For any additional investigations not explicitly mentioned in the original study protocol, a request for study amendment will be submitted to the relevant ethics committees.

### Data management and statistical analysis

A study specific database has been developed using a web-based Clinical Data Management System - Open Clinica®, for data entry and data cleaning, supervised by the lead data manager at LMU. All data collected at each performed visit must be entered in the respective electronic case report forms (eCRFs) provided in the data base.

The statistical analysis of this observational cohort study will be exploratory and use descriptive as well as inferential statistical methods. The statistical analyses will primarily be based on all enrolled patients with valid data available. Preliminary data sets will be analysed along the study in the frame of interim analyses, with the final analysis being completed once the database is locked.

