### Primary outcome and study endpoints

The primary outcome is a proportion of TB patients with severe pulmonary function impairment (restrictive, obstructive or mixed ventilation impairment), measured by spirometry at 24 months from TB treatment initiation and compared to national reference values. Long term lung function impairment is considered a clinically meaningful condition contributing to long term morbidity and mortality in former TB patients.

Amongst secondary outcomes are: the proportion of subjects with any impairment of pulmonary function as well as severity and type of impairment at TB diagnosis and 2, 6, 12 and 18 months; proportion of subjects with liquid and solid MTB culture conversion at different time points during or at the end of anti-TB treatment; the frequency of all-cause hospitalization episodes and all-cause mortality during follow-up of 24 months; the proportion of subjects with recurrent TB and; the proportion of subjects suffering from ongoing non-pulmonary comorbidities which are related to TB disease and treatment at different time points during 24 months of follow-up.

Studies regarding host immunology- and pathogen-associated risk factors and markers are planned as explorative, nested, case-control studies. Sample selection will be based on specific outcomes and risk factors present in the study participants.

Main outcomes studied in the context of socio-economic research are the proportion of subjects incurring catastrophic cost due to TB by the end of treatment; changes in income within follow up period; and scales for quality of life and general disability at treatment start, end of treatment and at follow-up. The cost of providing TB care and treatment, will be estimated from the health provider perspective, for both drug sensitive and drug resistant TB.

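### The valid-data analysis set makes the month-24 proportion describe survivors with usable spirometry, not all enrolled TB patients, and it will be too low if patients with worse lungs are more often missing

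*Protocol article*

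**What the plan says.** The Protocol article, section Data management and statistical analysis, sets the analysis population: "The statistical analyses will primarily be based on all enrolled patients with valid data available". It calls the analysis exploratory.

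The section Primary outcome and study endpoints defines the quantity of interest: "The primary outcome is a proportion of TB patients with severe pulmonary function impairment", measured by spirometry 24 months after treatment start and compared with national reference values. Death is not part of this outcome. It appears separately among the secondary outcomes as "all-cause mortality during follow-up of 24 months". The same section gives the reason for choosing the outcome: "Long term lung function impairment is considered a clinically meaningful condition contributing to long term morbidity and mortality in former TB patients".

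The Sample size section assumes a prevalence of 15% and says: "A sample size of 1.600 patients allows the estimation of the primary end point in the total cohort with a precision". The figure given there, for a 95% interval, is a half-width near 1.75 percentage points. It allows recruitment to be raised or lowered depending on how much usable endpoint data there are. It states no death rate, loss rate or rate of failed spirometry.

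Table 1 (Schedule of Events) schedules lung function at baseline and at months 2, 6, 9, 12, 18 and 24.

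**The concern.** The outcome is worded as a proportion of TB patients, but the analysis rule restricts it to those with a valid month-24 test. These are different populations if the reason for a missing test is related to lung function. The article's own rationale links impairment to morbidity and mortality, so it is plausible, though not established by the document, that patients with worse lungs are less likely to survive, return and complete an acceptable manoeuvre.

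The confidence interval would not show an error of this kind. The one response to incomplete endpoint data in the article is to change the number recruited. That narrows the interval around whatever the valid-data set estimates and leaves the selection as it was.

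The proportion is the study's headline result and is meant to support new estimates of TB disease burden and to inform guidelines. A figure for testable survivors, read as a figure for TB patients, could misstate that burden.

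**Working it through.** **Inputs from the Protocol article (Sample size).** Prevalence p = 0.15, N = 1,600, stated half-width about 1.75 points.

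**Inputs assumed, because the article gives none.** The rate of missing month-24 spirometry and its relation to severity. Both are varied below.

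**1. The stated precision.** Half-width = 1.96 × √[p(1 − p)/n].
- n = 1,600: 1.96 × √(0.15 × 0.85/1,600) = 1.75 points, as stated.
- The subgroup figures also reproduce: 2.47 points at n = 800 (stated 2.5) and 7.82 at n = 80 (stated 7.8).
- The 1.75 figure needs a valid month-24 test in all 1,600. With 10%, 20% or 30% missing (n = 1,440, 1,280, 1,120) it becomes 1.84, 1.96 or 2.09 points. This loss of precision is small. The selection is the larger matter.

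**2. Missingness that depends on severity.** Let a be the proportion missing among non-severe patients and r the factor by which severe patients are more often missing.

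Valid-data prevalence = p(1 − a·r) / [p(1 − a·r) + (1 − p)(1 − a)]

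With p = 0.15 and a = 0.20, the non-severe term is 0.85 × 0.80 = 0.68.

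| r | Severe, observed | Valid-data prevalence | Bias (points) |
|---|---|---|---|
| 0.5 | 0.15 × 0.90 = 0.135 | 0.135/0.815 = 16.6% | +1.6 |
| 1 | 0.15 × 0.80 = 0.120 | 0.120/0.800 = 15.0% | 0 |
| 1.5 | 0.15 × 0.70 = 0.105 | 0.105/0.785 = 13.4% | -1.6 |
| 2 | 0.15 × 0.60 = 0.090 | 0.090/0.770 = 11.7% | -3.3 |

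With a = 0.25, r = 1.5 and r = 2 give 12.8% and 10.5%.

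**3. The same question by overall missing fraction.** Let M be the fraction of the whole cohort without a valid test and Q the prevalence of severe impairment among them. With a whole-cohort prevalence of 15%:

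Bias = −M(Q − 0.15)/(1 − M)

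| M | Q = 10% | Q = 15% | Q = 22.5% | Q = 30% | Q at which the bias reaches -1.75 |
|---|---|---|---|---|---|
| 10% | +0.6 | 0 | -0.8 | -1.7 | 31% |
| 20% | +1.3 | 0 | -1.9 | -3.8 | 22% |
| 30% | +2.1 | 0 | -3.2 | -6.4 | 19% |

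The last column is 0.15 + 0.0175(1 − M)/M; for M = 20% this is 0.15 + 0.0175 × 4 = 0.22. At M = 5% the threshold is 48%.

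**4. Bounds without any assumption on Q.** If 15% is observed among those with valid data, the whole-cohort proportion lies between 0.15(1 − M) and 0.15(1 − M) + M: 13.5% to 23.5% for M = 10%, 12.0% to 32.0% for M = 20%, and 10.5% to 40.5% for M = 30%.

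Steps 2 to 4 make sense for patients whose month-24 lung function exists but was not validly measured. For patients who have died it is undefined, so these formulas do not quantify an error due to deaths.

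**The case against.** The strongest objection is that this is a short analysis paragraph in a journal article. The word for primarily leaves room for further analyses, valid data is not defined there, and imputation, weighting or sensitivity analyses may be in the full protocol or SAP, which are not shown. That stands as far as missing detail goes, and the absence of such detail is not the point made here. The point is that the primary population is already fixed in the article, and fixed as an available-case set.

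Four stronger readings are tempting, and the document supports none of them.

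- *The primary proportion will be understated by more than its precision.* Size and direction depend on quantities the article does not give. At r = 1.5 and a = 20% the bias is -1.6 points, inside the 1.75-point half-width; at 10% missing it stays inside for Q up to about 31%. Missingness unrelated to severity gives none, and loss of healthier patients reverses the sign. The sentence on mortality concerns the long term in former TB patients and does not say that severe impairment causes death or loss before month 24.
- *Leaving out the dead is an error.* A patient who has died has no month-24 spirometry, so this is a choice of target quantity, and mortality is a listed secondary outcome. With an assumed 10% mortality and 15% severe among survivors, dead or severely impaired is 0.10 + 0.90 × 0.15 = 23.5%, but that is a different outcome and not a correction of the 15%.
- *Risk-factor associations are pulled toward no effect.* If missingness depends only on the exposure, or only on the outcome, the complete-case odds ratio is unbiased. Attenuation needs a particular joint dependence that nothing in the article establishes.
- *The sample-size figures are wrong.* They reproduce. They simply presuppose complete endpoint data.

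**Conclusion.** The point holds in conditional form. By the stated rule, the month-24 proportion describes survivors who returned and produced valid spirometry, while the outcome is worded for TB patients. If those with worse lungs are more often missing, the proportion is too low. A plausible range for the bias is -1.6 to -3.3 points (20% missing among non-severe patients, severe patients missing 1.5 to 2 times as often, true prevalence 15%), so it may or may not exceed the 1.75-point half-width. A larger sample would not reduce it. These sizes rest wholly on assumed missingness. The article neither supports nor excludes them, and under other assumptions the bias is zero or upward. How deaths are treated is a choice of target that needs to be made explicit.

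**What to change.** In the analysis section or the SAP, before database lock:

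1. State the target population of the primary proportion, and say whether it is meant for all enrolled patients or for those alive at month 24.
2. Report month-24 status for all enrolled patients as dead, alive with severe impairment, or alive without it. Count patients of unknown vital status separately, so that the table adds up to the number enrolled.
3. For patients alive without a valid month-24 test, estimate the proportion by multiple imputation or inverse-probability weighting, using the spirometry already scheduled at baseline and months 2, 6, 9, 12 and 18, plus site, HIV and resistance status.
4. Show the valid-data estimate alongside, labelled as such, with the number missing and the reasons (lost, attended without a test, test not acceptable).

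A composite of death or severe impairment may be added if wanted, presented as a separate outcome.

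The cost is about a paragraph of text and modest extra analysis, with no new data. The limitation is that imputation or weighting relies on a missing-at-random assumption given the earlier measurements, which is weakest for patients lost early or never able to perform the test. The none-to-all bounds in step 4 of the working are a simple way to show how much rests on it.

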### Study monitoring

Study activities related to data generation, recording and management processes will be monitored on a regular basis. Two external monitors from coordinating institutions have been assigned to this task. These clinical monitors will follow the study closely, visit the sites at regular intervals and will be in contact by phone and written communication, as required. In addition to close supervision by the external monitors as well as by a local supervisor, one internal clinical monitor is supervising the procedures in the study clinics at each study site in the context of a continuing clinical monitoring training which includes workshops and distance learning modules. Additionally, an External Advisory Board consisting of six representatives of NTPs, local and international policy makers as well as relevant (clinical) scientists in the field of TB research was created to regularly evaluate the study activities and research progress as well as support the process in scientific decision making with regards to the global TB research agenda.

### Ethical considerations

This study is performed in accordance with the study protocol, the Declaration of Helsinki (October 2013) and the WHO Handbook for Good Clinical Research Practice (July 2002) as well as any other applicable national and other regulatory guidelines. The protocol, Informed Consent Form (ICF), eCRFs and other relevant study documents were reviewed and approved by all respective Ethical Committees at each study site and also at coordinating institutions. All participants sign an ICF prior to enrolment in the study. For each enrolled subject, we will assign a unique study identification number, which will be used to identify the subject’s data and sample within the project. The eCRFs and other study documents do not include any identifying information linked to the study ID in order to maintain confidentiality for all records and data of the participants.

## Discussion

Current guidelines do not foresee specific monitoring or treatment of pulmonary injury related to TB, nor has disability due to long term loss of lung function or other sequelae been included in current global estimates of the total burden of disease. Social support for TB patients rarely consider the period after cure has been declared. As NTP in most countries do not follow up patients after “cure”, the extent of the long-term complications and their impact on individuals and households so far remain unknown.

The present lack of knowledge regarding the pathogenic mechanisms or clinical co-factors causing adverse outcomes in TB hinders the development and evaluation of interventions to reduce the overall TB disease burden or costs related to TB. Additionally, the lack of current, geographically relevant information about the economic impact of TB and the likely costs to national health systems pose an obstacle to efficient resource allocation both within TB programs and across competing health and social care priorities. Studies, such as TB Sequel, examining long term disability and associated risk factors, income loss, and treatment-related costs are crucial to inform the policy changes needed to address poor long-term TB outcome and catastrophic costs burden. Compared to other TB cohort studies TB Sequel will follow patients for at least 24 months which enables us to report lung outcome when any impairment related to TB disease has stabilized, thus when it can be assumed to have become chronic. Likewise the characteristics of ongoing socio-economic consequences and disease burden can be studied in those patients with relevant chronic lung or other TB related injury for at least 24 months. This allows for new estimates of TB disease burden which go beyond microbiological cure. Due to sample size and selection of different study sites across Africa we will be able to describe the influence of important potential risk factors on lung outcome such as infection with an MDR-TB strain, HIV-coinfection and comorbidities like COPD and diabetes but also the relevance of different genetic and socio-economic background. On the other hand, the follow-up of only 24 months precludes the investigation of interrelation of pulmonary TB with pre-existing and especially newly developed comorbidities as well as the influence of TB on long term survival and socio-economic status. Another limitation of the study is that the investigators have no influence on the composition of and adherence to anti-TB (and anti-retroviral) treatment and individual treatment regimens might have a different influence on lung outcome. On each study visit, co-medication and drug adherence are documented in order to enable sub-group analyses as well as to control for it during analysis of other risk factors for poor treatment outcomes. Finally, the capacities for adequate treatment and follow up for the majority of diagnosed comorbidities are currently limited or even not available at most study settings.

Thus, the TB Sequel Project is an integral part of an overall strategy to fill a knowledge gap needed to improve TB treatment and outcomes globally. It is an interdisciplinary project that combines multiple components: research, capacity building and translation of evidence into policies. All research sites will receive training and are included in capacity building activities (both in human resources and infrastructure) which creates an enabling environment for research and increases competencies in diagnosis and management of TB and lung health with direct benefit for future TB patients.

